## 5. Discussion

It is our understanding that there have not been any previous clinical trials or case studies conducted to determine the effects of VR-based interventions on preoperative pain and anxiety among neurosurgical patients. Preoperative anxiety has detrimental consequences as it raises postoperative complications, behavioral disorders, and can be disturbing emotionally.

Preoperative anxiety may occur due to multiple factors, such as former negative experiences, being exposed to terrifying stereotypes of doctors in the media, or even triggered by friends, family members, and colleagues [46]. Some common fears linked to preoperative anxiety are the fear of pain itself, blood injuries, and hospital settings. Milgrom et al. revealed four groups of anxiety-driven patients based on the origins/sources of the patients’ fear. Some were anxious due to specific surgical stimuli, distrust of hospital workers, general dental anxiety, and fear of the unknown. It was discovered that more invasive types of stimuli were more anxiety-provoking; however, stimuli linked to clinic offices, team members, and/or the equipment being used were the least fear-provoking. It was revealed that most of the patients felt anxious during their first clinical visit. Their main concerns were how anesthesia would be administrated, extraction, feelings of numbness, and the root canal treatment itself [47]. Recent research has connected anxiety with pain as it increases sympathetic activity, thereby releasing endogenous adrenaline and increased pain through nociceptors [48].

Chaves et al. surmised that there were no major differences between blood pressure (BP) and anxiety for either gender [49]. Conceição et al. found no statistically significant differences in heart rate (HR) and BP of anxious and non-anxious patients [50].

The purpose of this research is to further explore the beneficial impacts of VR on alleviating preoperative anxiety and levels of pain by examining three study groups. Prior reports have indicated that VR intervention can lessen the anxiety experienced by patients before surgery; however, other studies have found no such benefits among adult patients. Additionally, digital distraction techniques have been proven to lower stress and pain levels during interventions and painful procedures.

Consequently, distraction techniques and non-pharmacological methods are paramount for simple, easily implementable interventions that can reduce anxiety and disruptive behaviors among patients. VR is a significant advancement in modern technology to simulate reality, transforming the philosophical concept of the virtual world into a practical experience [51]. It is a new medium that surpasses mere illusion and can produce real-world results due to its unlimited potential for large-scale applications in not only training and treatment, but also therapy. VR not only helps to visualize events but also to experience psychological conditions and personalized perceptions, fostering a sense of ownership, presence, and immersion [52,53]. It can also influence physical sensations during interventions, including stress and anxiety reduction and pain management, while inducing the necessary emotions [54,55].

Virtual reality headsets and related devices used for patients about to undergo surgical intervention, such as spinal stabilization, laminectomy, discectomy, and stimulation, can help to reduce acute pain and anxiety, leading to higher levels of patient satisfaction. Various other non-pharmacological approaches have been employed to lessen anxiety, stress, and pain, such as gamification, watching cartoons, and art music therapy. Gamification and preoperative multimedia education are two other resources that may be effective throughout the preparation phases before surgery and in postoperative care. Studies have outlined that children who undergo an education-based multimedia intervention are less anxious and stressed about surgery and other hospital procedures.

In spite of the significant pain and anxiety experienced by many patients prior to undergoing a surgical procedure, non-pharmacological approaches are still seldomly implemented as a means or tool for reducing anxiety or pain-related signals. VR video intervention is able to lessen preoperative anxiety while providing the chance to teach and familiarize patients in the hospital environment, be it for an inpatient or even at home, before attending for surgery. VR can also improve the physical, mental, and emotional state of each patient.

Sato et al. investigated the use of VR for the treatment of complex regional pain syndrome in patients and was able to halve the pain intensity scores [56]. This correlates with our study, wherein a significant reduction in the postoperative pain perception of the patient was observed. Sarig-Bahat et al. used VR to treat 67 patients with chronic neck pain and discovered that VR usage for a single session raised the cervical range of motion and lessened neck pain [57]. Hoffman et al. used VR for physical therapy sessions for burn victims and discovered that the perception of pain for his patients was considerably less when using VR, which confirms the results of our study [13]. In a simulation study conducted by Tanja-Dijkstra et al., it was revealed that the use of VR as a means of distraction can potentially influence a patient’s perception of an anxiety-inducing procedure [58]. Jeffery I Gold et al. concluded that VR usage lowers anxiety by preventing vivid memories from being formed [59]. Conversely, although the pros of VR intervention seem significant, not much is known surrounding the longer-term effects, such as after surgery, during hospitalization or after discharge.

This study delved into the effectiveness of distractions and immersion-based virtual reality in the context of preoperative anxiety among patients undergoing spinal surgery. Using virtual reality to lessen or distract attention away from the hospital environment seems to allow patients to tolerate preoperative anxiety. The VR exposes patients to worrying and unfamiliar situations in a safe environment before the real procedure takes place. This technique/intervention can result in a sensation of familiarity and, thus, result in reduced anxiety.

## Figures and Tables

**Table 1 brainsci-16-00587-t001:** Eligibility Criteria for Study Enrollment.

Inclusion Criteria	Exclusion Criteria
Adult patients between 18–70 years old Patient’s admission prior to surgery day (at least 1 day) Patients’ first surgery with no prior surgical history cervical vs. lumbar vs. thoracic) Type of spine surgery (e.g., cervical vs. lumbar vs. thoracic) Surgical approach (e.g., minimally invasive vs. open) Anesthetic technique (e.g., general) Expected hospital stay—2 days Capable of providing informed consent and participate in the study follow-up questionnaire Patients speak English	Congestive heart failure, hypertension and anti-hypertensive medications Adrenal insufficiency Cognitive impairment (evaluated by MMSE, MoCA) Cerebrovascular diseases, ophthalmological diseases (strabismus, diplopia, retina degeneration, glaucoma), neurological conditions (epilepsy or seizure, dementia, vertigo, dizziness, motion sickness)—evaluated by: history taking, examination, vision test (Ishihara test) Auditory impairment Psychiatric illness (schizophrenia, bipolar disorder, psychotic depression)—(evaluated by MINI questionnaire) Patients with neuropathic pain Use of sedative drugs, anti-depressants, anxiolytics, and anti-epileptic drugs Claustrophobia GCS < 15

**Legend:** MMSE, Mini-Mental State Examination; MoCA, Montreal Cognitive Assessment; MINI, The Mini International Neuropsychiatric Interview; GCS, Glasgow Coma Scale.

**Table 2 brainsci-16-00587-t002:** Primary and secondary outcome assessment.

Timepoint	Assessment	Measures
Day before surgery (pre-VR)	Baseline	STAI-S, VAS pain
Day before surgery (post-VR)	Immediately after VR intervention	STAI-S, VAS pain, patient experience satisfaction
Within 24 h after surgery	Postoperative	VAS pain, analgesic use

**Table 3 brainsci-16-00587-t003:** Preoperative and postoperative psychometric scales.

Baseline Values
Patients’ demographics: age, sex, education, medical history (comorbidities), medication, surgery type, duration, ASA status Anxiety (STAI-S) Stress (PSS-10) Depression (BDI-II) Pain score (VAS) Satisfaction (EVAN-G) Cognitive (ACE-III) Personality test (PID-5) Postoperative analgesia (Medical charts and records)

**Legend:** ASA, American Society of Anesthesiologists; STAI-S: State-Trait Anxiety Inventory Scale; PSS-10, Perceived Stress Scale; BDI-II, Beck Depression Inventory; VAS, Visual Analogue Scale; EVAN-G, Evaluation du Vecu de l’Anesthesie Generale; ACE-III, Addenbrooke’s Cognitive Examination; PID-5, Personality Inventory for DSM-5.

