## 3. Objectives

The aim of this research study is to evaluate the impact of immersive VR exposure on preoperative anxiety and pain, and, additionally, to assess whether VR intervention would significantly alleviate pain and anxiety levels of patients undergoing complex spinal surgeries. We hypothesize that the application of preoperative VR-based intervention will alleviate anxiety and pain both pre- and postoperatively when it is used as treatment to complement standard care compared to standard routine care alone, and that it may lead to better outcomes and higher satisfaction in patients. The primary objective is to evaluate whether procedural/educational VR reduces preoperative anxiety compared with standard care. Secondary objectives include comparing relaxation/distraction VR versus standard care, and procedural/educational VR versus relaxation/distraction VR with respect to postoperative pain, analgesic use, and patient satisfaction.

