## 4. Material and Methods

### 4.1. Trial (Study) Design

This is a single-center study prospective, randomized, placebo-controlled trial with three parallel groups of adult patients (18 to 70 years) who have degenerative spinal disorders, specifically those diagnosed with lumbar or cervical spondylosis who are scheduled to undergo spinal fusion, discectomy, decompression, or stabilization procedures. Relevant surgical variables, including cervical/lumbar/thoracic location, type of surgery, surgical approach, duration of surgery, and perioperative complications, will be prospectively recorded and considered in adjusted analyses. The study assesses the influence of a single preoperative VR (exposure) session and its effect on both preoperative and postoperative anxiety and pain, as well as reported functional outcomes in patients undergoing elective spine surgery.

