#### 4.7.4. Clinical Outcome Variables and Assessment

The primary outcome is the change in STAI-S score from baseline to immediately after intervention. Secondary outcomes include postoperative pain intensity assessed using the Visual Analogue Scale (VAS), postoperative analgesic use, patient satisfaction, and VR-related adverse effects. These outcomes will be measured preoperatively on the day before surgery, before the VR content exposure, and after. Measurements will be made again postoperatively—within 24 h. Preoperative and postoperative STAI-S and VAS will be compared for data analysis.

The baseline assessment is conducted one day before surgery, prior to the VR intervention, to capture the patient’s preoperative state under conditions closest to the actual surgical context. We believe this timing best reflects the anxiety and pain levels that the VR intervention aims to reduce. The postoperative assessment within 24 h is intended to evaluate the immediate effect of the intervention on perioperative anxiety and pain, which is the primary focus of our study. We acknowledge that longer-term outcomes may differ, but these are beyond the scope of the current trial, which specifically targets the short-term perioperative period (see Table 2).

The secondary outcome will be the patients’ quality of life and satisfaction (EVAN-G) of the VR intervention, time spent thinking about pain assessed, and postoperative analgesics measured from patient treatment charts within 24 and 48 h postoperatively and used for data analysis, as the level of satisfaction and thinking time spent on pain can contribute to an increased perception of pain.

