### 4.9. Statistical Analysis

The statistical analysis will be performed under the mentorship of a biostatistician experienced in neurosurgical research. The nominal data will be presented as *n* (% of the total). The dependencies between them will be assessed using the test chosen based on the size of the smallest sample. All analyses will follow an intention-to-treat approach. The primary endpoint (change in STAI-S score from baseline to immediately postintervention) will be analyzed using one-way ANCOVA adjusted for baseline STAI-S. Pairwise comparisons will be Bonferroni-corrected. Secondary outcomes will be analyzed as follows: VAS pain at 24 h (ANCOVA adjusted for opioid dose), total opioid consumption (ANOVA or Kruskal–Wallis depending on distribution), patient satisfaction (Kruskal–Wallis), and rescue analgesic use (χ^2^ test). Longitudinal measures (baseline → post-VR → postoperative) will be evaluated with a linear mixed-effects model including group, time, and group × time interaction. Normality will be tested using the Shapiro–Wilk test. Missing data will be assessed for pattern and mechanism. Multiple imputation (m = 10) will be used if appropriate. Longitudinal analyses will primarily rely on linear mixed-effects models, which are robust to missing observations under missing-at-random assumptions. The primary comparison will evaluate procedural/educational VR versus standard care with respect to STAI-S score change. Secondary comparisons will include relaxation/distraction VR versus standard care and procedural/educational VR versus relaxation/distraction VR. Postoperative pain analyses will additionally be adjusted for perioperative opioid consumption and surgery duration when appropriate. Statistical analysis will be performed using STATISTICA 13.1 (TIBCO, Palo Alto, Santa Clara, CA, USA) and two-sided α = 0.05.

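### Table 2 schedules no STAI-S after surgery, which contradicts the hypothesis, the design statement and the outcomes section; the conflict should be settled before data are lost

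*Protocol article*

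**What the plan says.** Three places in the protocol article commit to anxiety after surgery.

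- Section 3 (Objectives) hypothesises that preoperative VR "will alleviate anxiety and pain both pre- and postoperatively".
- Section 4.1 (Trial Design) says the study assesses the session and "its effect on both preoperative and postoperative anxiety and pain".
- Section 4.7.4 (Clinical Outcome Variables and Assessment) lists the outcomes with STAI-S first, then says "Measurements will be made again postoperatively—within 24 h" and "Preoperative and postoperative STAI-S and VAS will be compared for data analysis". It also gives perioperative anxiety, alongside pain, as a purpose of the 24 h assessment.

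Section 4.9 (Statistical Analysis) adds that "Longitudinal measures (baseline → post-VR → postoperative) will be evaluated with a linear mixed-effects model", without naming the outcomes.

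The schedule differs. Table 2, to which Section 4.7.4 refers the reader, gives STAI-S and VAS pain at baseline, "STAI-S, VAS pain, patient experience satisfaction" immediately after VR, and "VAS pain, analgesic use" in the first 24 h after surgery.

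**The concern.** A state-anxiety score is a self-report about the moment at which it is taken. Analgesic use can be read from the chart afterwards; an anxiety score that was not asked for in the first 24 h cannot be obtained later. If the people running the assessments work from Table 2, the trial would end with a stated hypothesis and a planned comparison for which nothing had been recorded, and each patient assessed in that way would be a permanent loss.

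The measure also has no settled status. It is neither a named secondary outcome nor clearly absent from the plan, so a reader of the results could not tell whether a reported (or unreported) postoperative anxiety comparison had been planned.

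**Working it through.** No stated figure is in dispute. The check sets the passages side by side and counts time points.

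**Places that call for postoperative STAI-S or postoperative anxiety**

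- Section 3, hypothesis: yes, for anxiety.
- Section 4.1, design statement: yes, for anxiety.
- Section 4.7.4, repeat measurement and planned comparison: yes, with STAI-S named.
- Section 4.9, longitudinal model: a postoperative time point is named, the outcome is not.

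**Places that leave it out**

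- Table 2, postoperative row: VAS pain and analgesic use only.
- Section 4.7.3: postoperative collection is described for analgesic use and pain, not anxiety.
- Secondary outcomes in the Abstract and Section 4.7.4, and secondary objectives in Section 3: pain, analgesic use, satisfaction and, in the outcome lists, VR adverse effects and a few further items. Postoperative STAI-S is in none of them.
- Section 4.9, outcome-by-outcome list of secondary analyses: no test for postoperative STAI-S.

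Table 3 does not decide the matter. Its title mentions both periods, but the only heading inside it is for baseline values.

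**Count of time points**

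- STAI-S in Table 2: 2 (pre-VR, post-VR).
- STAI-S under Section 4.7.4: 3 (pre-VR, post-VR, postoperative).
- VAS pain in Table 2: 3.

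The table therefore treats the two measures differently, and the gap is specific to STAI-S.

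**Consequence for the data**

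Planned enrolment is 3 arms × 50 = 150 (Section 4.3.1). Before attrition:

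- under Section 4.7.4: 150 × 3 = 450 STAI-S scores;
- under Table 2: 150 × 2 = 300 STAI-S scores;
- difference: 450 − 300 = 150, which is every postoperative score.

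**Consequence for the analysis**

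For a model with group, time and their interaction, the interaction has (groups − 1) × (times − 1) degrees of freedom.

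- Three time points: (3 − 1) × (3 − 1) = 4.
- Two time points: (3 − 1) × (2 − 1) = 2.

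Under Table 2, the two STAI-S interaction contrasts that involve the postoperative time cannot be estimated. The two that remain concern the change from baseline to just after the session, which is the question the primary ANCOVA already answers. Neither device for missing data in Section 4.9 helps. Multiple imputation and the missing-at-random property of mixed models both need the time point to have been observed in some patients.

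For VAS pain, all three time points are scheduled, so the four-degree-of-freedom interaction stands.

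**The case against.** The strongest reply has four parts.

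1. Section 4.7.4, read alone, does provide for a postoperative STAI-S. Nothing says that Table 2 overrides it. **This stands.** A reader might infer that the trial will certainly have no postoperative anxiety data; the document shows two conflicting statements and does not establish which one the site will follow.

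2. Table 2 is visibly not a full schedule. It omits PSS-10, BDI-II and the baseline EVAN-G (Section 4.8), the analgesic assessment out to 48 h (Sections 4.5 and 4.7.4) and VR adverse effects (Section 4.5). The article is also a condensed account of a protocol that is not shown. **This stands in part.** It is a reason for caution about what will happen on site. It does not remove the contradiction, because the table is presented as the assessment of primary and secondary outcomes, lists STAI-S in two of its three rows, and is backed by Section 4.7.3. This is a disagreement between statements that are both in the article, not detail left to a fuller document.

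3. The longitudinal model names no outcome, so a reader might infer too much in saying that it needs a postoperative STAI-S or cannot be fitted. **This stands.** The model can be run as written for VAS pain. That it also covers STAI-S is implied by the comparison in Section 4.7.4 but not stated in Section 4.9.

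4. Postoperative anxiety is not the primary objective and is not a listed secondary outcome. **This stands**, and it limits the severity. It also shows that the inconsistency goes beyond one table cell: the outcome lists side with the table, while the hypothesis, the design statement and the comparison sentence side against it.

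**Conclusion.** The contradiction is real. Conditional on Table 2 being followed, 0 of 150 patients have a postoperative STAI-S, the postoperative part of the anxiety hypothesis is untestable, and a STAI-S mixed model is reduced to two time points.

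It would be wrong to infer that the primary analysis is at risk. The primary endpoint is the STAI-S change across the VR session. It uses only the two preoperative scores, both of which Table 2 schedules, so its ANCOVA and the sample size are untouched. The listed secondary outcomes are not affected either.

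This is an internal inconsistency that should be fixed, and early, because the loss cannot be repaired for patients already assessed. It is not a defect that invalidates the trial. The conclusion assumes only that the table and the text mean what they say; it does not depend on any effect size, standard deviation or attrition rate.

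**What to change.** Choose one of two routes and apply it throughout.

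**Keep postoperative anxiety.** Add STAI-S to the postoperative row of Table 2 for all three arms, at the same assessment as the VAS. Bring the sentence on postoperative data in Section 4.7.3 into line. Name postoperative STAI-S as a secondary outcome in the Abstract and Section 4.7.4. In Section 4.9, state which outcomes the longitudinal model covers.

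**Drop it.** Remove postoperative anxiety from the hypothesis in Section 3, the design statement in Section 4.1, and the repeat-measurement, comparison and purpose sentences in Section 4.7.4. In Section 4.9, limit the three-time-point model to VAS pain.

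The first route costs one short questionnaire at an assessment that already takes place, a small burden for a patient on the day after surgery. The second needs only edits to the text, but gives up part of the stated hypothesis. Neither changes the sample size or the primary analysis. Patients already assessed without a postoperative STAI-S should be counted and reported.

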## Data Availability

No new data were created or analyzed in this study.
